### Masking (Blinding)

The study is single-blind; both the outcome assessor and the statistician performing data analysis will remain blinded to group allocation. Participants will be instructed not to disclose details of their intervention to the assessor. The success of blinding will be evaluated at the end of the trial by asking the assessor to guess each participant’s group assignment, and the results will be reported.

### Data Management

All participant data will be recorded on paper case report forms and stored in locked cabinets in the University of Almería outpatient clinic. Digital data will be entered into a password-protected SPSS software database.

Data entry will be double-checked for accuracy by the data manager. Backups of digital data will be maintained on a secure university server. Only authorized personnel (principal investigator, statistician, and outcome assessor) will have access to identifiable participant data.

Data will be retained for a minimum of 10 years following completion of the study, in accordance with university and national regulations.

### Adverse Event Monitoring and Management

An adverse event is defined as any undesirable and unintended sign, symptom, or medical condition occurring in a participant following receipt of a study intervention, regardless of whether a causal relationship with the administered treatment exists.

To date, no significant risks have been reported for any of the interventions; however, minor adverse effects—such as a temporary increase in pain or the development of bruising—may occur, which can be minimized through the physiotherapist’s anatomical knowledge and clinical experience.

All adverse events will be carefully monitored and recorded throughout the study. The physiotherapists responsible for the intervention will document the nature, intensity, duration, and potential causes of each adverse event, as well as any corrective actions taken.

If a significant adverse event is identified, the need to temporarily or permanently suspend the intervention for the affected participant will be assessed immediately, following predefined safety criteria. The ethics committee and the principal investigator will be notified of any serious adverse events in accordance with applicable regulatory guidelines.

Participants will also receive continuous information on the prevention and management of possible minor side effects and will be encouraged to report any new or unexpected symptoms immediately. These measures are intended to ensure participant safety and maintain the integrity of the study.

### Interim Analyses and Stopping Guidelines

No formal interim analysis is planned due to the short duration and minimal risk of the interventions. However, the study may be suspended for any participant in the event of serious adverse events, as determined by the principal investigator in consultation with the Research Ethics Committee.

### Safety Considerations

All patients and physiotherapists will receive specific information about the study in writing and will have a chance to discuss the procedures with a member of the study team before providing consent to participate. They will also be informed that they can withdraw from the study at any time. Participants who agree to participate in the study will sign 2 copies of the informed consent form, one that will be kept in the trial records and one for the participant.

The data collected from each patient will be stored in a closed locker in an office at the University of Almería, and only the physiotherapists evaluators will have access to that information. Subsequently, the data will be entered and saved by the statistician on a password-protected laptop to maintain confidentiality. Eligibility criteria, results, and analyses will not be modified after registration of the first participant.

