To minimize treatment variability, all therapists will follow a standardized intervention manual detailing patient positioning, trigger point identification, needle placement procedures, stimulation parameters, and safety precautions [31,32,35]. A treatment record form will be completed after each session documenting the muscles treated, number of needles inserted, stimulation intensity, treatment duration, and any adverse events.

Participants will be informed about the possibility of postneedling soreness and will be instructed to apply local cryotherapy if required during the first 48 hours. A follow-up telephone call will be conducted 48 hours after each treatment session to monitor adverse events and ensure participant safety.

Immediately after EDN, participants will perform the same cervical-specific therapeutic exercise program received by the control group. Therefore, this trial is designed to evaluate the added value of incorporating EDN into an exercise-based physiotherapy program rather than isolating the specific physiological effects of EDN itself.

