### Data Analysis

Data will be analyzed using SPSS (version 28.0; IBM Corp) and will follow the intention-to-treat principle, whereby all randomized participants will be analyzed in the groups to which they were originally assigned, regardless of treatment adherence or completion. Additionally, a per-protocol analysis will be conducted including participants who complete at least 80% (5/6) of the in-person treatment sessions. All analyses will be conducted by a statistician blinded to group allocation.

Descriptive statistics will be calculated for all variables. Continuous variables will be presented as mean (SD) or median (IQR), depending on the data distribution, while categorical variables will be expressed as frequencies and percentages.

Baseline comparability between groups will be assessed using independent Student *t* tests for normally distributed continuous variables, Mann-Whitney *U* tests for nonnormally distributed variables, and chi-square tests for categorical variables. Normality will be evaluated using the Kolmogorov-Smirnov test and visual inspection of histograms.

A statistically significant group × time interaction will be interpreted as evidence of differential treatment effects over time. To evaluate the effects of the intervention over time and between groups, linear mixed-effects models will be used, including group (experimental vs control), time (baseline, postintervention, and 2-mo follow-up), and the group × time interaction as fixed effects, with participants included as random effects. This approach allows appropriate handling of repeated measures and missing data.

If model assumptions are not met, appropriate nonparametric alternatives (eg, Friedman test for within-group comparisons and Mann-Whitney *U* test for between-group comparisons with adjusted post hoc analyses) will be applied. Adjustment for multiple comparisons among secondary outcomes will be performed using the Holm-Bonferroni procedure.

Missing data will be handled using multiple imputation methods under the assumption of missing at random. Sensitivity analyses will be conducted to assess the robustness of the findings. Dropouts and losses to follow-up will be reported and compared between groups. Twenty imputed datasets will be generated using multiple imputation procedures.

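### The data-entry and access roles are not reconciled with the claimed blinding of the statistician, so that blinding is not secured as written

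*Protocol article*

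**What the plan says.** Two sections claim a blinded analyst. Data Analysis states: "All analyses will be conducted by a statistician blinded to group allocation". Masking (Blinding) states that "both the outcome assessor and the statistician performing data analysis will remain blinded to group allocation".

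Two other sections give the statistician work and access that bear on that claim:

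- Safety Considerations, on the data collected from each patient: "the data will be entered and saved by the statistician on a password-protected laptop".
- Data Management, on the scope of the forms: "All participant data will be recorded on paper case report forms".
- Data Management, on access: "Only authorized personnel (principal investigator, statistician, and outcome assessor) will have access to identifiable participant data".
- Safety Considerations, also on access: "only the physiotherapists evaluators will have access to that information".
- Data Management, on checking: "Data entry will be double-checked for accuracy by the data manager".

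The section on the EDN plus exercise arm describes a form completed after each session, "documenting the muscles treated, number of needles inserted, stimulation intensity, treatment duration, and any adverse events". The same section requires the final current in mA to be recorded at every session.

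**The concern.** The role declared blinded is also the role assigned to transcribe the participant data. Needle counts and current intensity have no counterpart in an exercise-only arm. Whoever enters them learns who received EDN and, by elimination, who did not, even if no group label appears on the form.

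The Randomization section says that participants and treating physiotherapists cannot be blinded, so masking of the assessor and of the statistician is all the masking the trial claims. Masking (Blinding) plans a check of blinding for the assessor only, so a lapse at the statistician would not show up.

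Some decisions are left until the data are seen: covariates to be explored if baseline imbalance is found, nonparametric alternatives if assumptions fail, and sensitivity analyses that are not specified. The protocol does not itself tie blinding to these decisions, but they are where an analyst's knowledge of the arm could matter.

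**Working it through.** No arithmetic applies. The check is to set the statements side by side and see whether one reading satisfies all of them.

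1. **Who must be blind.** The person who analyses the data (Data Analysis; Masking).
2. **Who enters the data.** The statistician, without qualification (Safety Considerations). The Randomization section mentions an independent statistician, but only for creating the sequence. The only continuing statistical role described is the analyst, and no sentence separates data entry from analysis.
3. **What is entered.** Safety Considerations speaks of the data collected from each patient. Data Management says that all participant data are on paper forms. Neither excludes any form.
4. **Which fields reveal the arm.** Needles inserted, muscles treated by needling, and current intensity. Adverse events as such do not: the adverse event section and Table 2 have them monitored in both arms. A treatment record as such does not either, because the Participants section plans standardized records for the whole study. It is the needling fields that identify the arm.
5. **Who may see the data.** Safety Considerations limits the stored data to the evaluating physiotherapists, while Data Management lists the principal investigator, the statistician and the outcome assessor. These do not agree. The data manager is on neither list, although checking entry presumably requires sight of the forms.

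Two readings follow.

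- **Narrow reading: only the evaluators' outcome forms are entered by the statistician.** Blinding can then hold. But the per-protocol analysis needs attendance, which the treating therapist records, so some therapist-side data must reach the database. No one other than the statistician is named to enter it. Attendance alone would not reveal the arm, but the session form might.
- **Wide reading: all forms are entered by the statistician.** The needling fields pass through the analyst's hands and the claimed blinding fails. If the outcome assessor can open the same files, the assessor's blinding is at risk as well.

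The protocol does not say which reading applies. A masked group code would not settle the matter by itself, because needling fields left in the dataset would identify the arm behind the code.

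**The case against.** The strongest defence is the sentence just before the data-entry sentence, which restricts the stored data to the evaluators. On that reading, what is later entered is the evaluators' own material, namely outcome forms that need not show the arm. Session records are completed by treating staff and could be kept apart. Entering data does not in itself unblind anyone, and seeing a participant's identity is not the same as seeing the allocation. This stands as far as it goes. It shows that a consistent arrangement is possible, but not that the protocol has adopted it, since Data Management uses wider wording on both scope and access.

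A second defence is that masked codes and separate files are commonly left to a data-management plan or statistical analysis plan that is not shown. That is fair, and their absence from an article is not the point. The point is that the article itself assigns data entry to the role it declares blinded.

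A third defence is prespecification. The article names the linear mixed model and fixes the primary end point and its time. Safety Considerations adds that analyses will not be modified after the first participant is registered. This stands, and it limits the severity.

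Two stronger readings are tempting. A reader might infer that statistician blinding is broken. The documents do not support that, because no passage says that the statistician receives the allocation or enters the needling records. A reader might also try to express the cost as an inflated false-positive rate from choosing the most favourable of several tests. The smallest of several two-sided p-values is the same when the arm labels are swapped. Such a figure would measure analytic flexibility, which an analyst holding masked codes has as well, and not the effect of unblinding.

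**Conclusion.** The point holds as an unreconciled assignment of roles. Data Management and Safety Considerations do not fit the blinding stated in Data Analysis and Masking (Blinding), and the two access statements do not fit each other. Statistician blinding is therefore not secured as written, and under the Data Management list the assessor's blinding is open to the same doubt.

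The severity is minor to moderate and no figure can be put on it. The conclusion rests on two assumptions: that the unqualified references to the statistician mean the analyst, and that the session records belong to the participant data held on the paper forms. Both are the natural reading, but neither is stated outright.

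**What to change.** - Change Safety Considerations so that the data manager or other non-analysis staff enter the forms. Someone other than the person who entered them should do the entry check. If the data manager takes over entry, the check now assigned to the data manager moves to another person.
- Keep the needling session records out of any file open to the analyst or the outcome assessor.
- Give the analyst a dataset with a masked group code and no needling fields until the primary analysis is complete.
- Rewrite the Data Management access list and the access sentence in Safety Considerations so that they agree with each other and with the two blinding statements.
- Data collection was expected to end by March 31, 2026, so entry may already have taken place. If the statistician has entered records that show needling, say so in the trial report and qualify the blinding claim.

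The cost is a few sentences, one reassigned task and slightly more data handling. No new staff are needed for entry, since a data manager is already named.

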### Follow-Up

The recruitment of patients started on November 1, 2025, and was completed by December 31, 2025. All follow-up data are expected to be collected by March 31, 2026. Data analysis, manuscript preparation, and submission to peer-reviewed scientific journals will be carried out during 2026 (Table 2).

**Table 2. T2:** SPIRIT (Standard Protocol Items: Recommendations for Interventional Trials) schedule of enrollment, interventions, and assessments^a^.

Study period (time point)	Screening (before allocation)	Baseline (week 0)	Week 1 (session 1)	Week 2 (session 2)	Week 3 (session 3)	Week 4 (session 4)	Week 5 (session 5)	Week 6/postintervention (session 6)	2-mo follow-up (2 mo after intervention)
Enrollment									
Eligibility screening	✓								
Informed consent	✓								
Baseline demographic and clinical data		✓							
Allocation		✓							
Interventions									
Electrical dry needling + therapeutic exercise			✓	✓	✓	✓	✓	✓	
Therapeutic exercise only			✓	✓	✓	✓	✓	✓	
Assessments									
Neck Disability Index		✓						✓	✓
Visual Analog Scale		✓						✓	✓
McGill Pain Questionnaire		✓						✓	✓
SF-36^b^ Health Survey		✓						✓	✓
Tampa Scale for Kinesiophobia		✓						✓	✓
Cervical range of motion		✓						✓	✓
Pressure algometry at MTrPs^c^		✓						✓	✓
Pittsburgh Sleep Quality Index		✓						✓	✓
Pain Catastrophizing Scale		✓						✓	✓
Cervical isometric strength		✓						✓	✓
Cervical flexor endurance		✓						✓	✓
Adverse event monitoring			✓	✓	✓	✓	✓	✓	✓

a This table summarizes the schedule of enrollment, allocation, interventions, and assessments. Screening and informed consent occur before allocation. Baseline assessment and randomization are performed at week 0. The intervention period consists of 6 weekly sessions, and outcomes are assessed at baseline, immediately after the sixth session, and at 2-month follow-up.

b SF-36: Short Form-36 Health Survey.

c MTrPs: myofascial trigger points.

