### Sample Size Calculation

The sample size was calculated for the primary outcome, the NDI, based on detecting a clinically meaningful between-group difference of 7.5 points, which is consistent with previous studies on the responsiveness of the NDI. Assuming a standard deviation of 10.58 points, a 2-sided significance level of .05, and 80% statistical power, the required sample size was 32 participants per group. To account for an anticipated 10% (3/32) loss to follow-up, the final target sample size was increased to 35 participants per group, resulting in a total sample of 70 participants.

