## Results

This study was funded in 2023 by the Fundación Progreso y Salud (reference AP-0429‐2023-C4-F2). Participant recruitment was conducted between November 1, 2025, and December 31, 2025. As of January 2026, 35 of the planned 70 participants had been recruited. Data collection for all outcome measures is expected to be completed by March 31, 2026. Data analysis, interpretation, and manuscript preparation will be carried out during 2026. The results of the trial are expected to be submitted for publication in late 2026.

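### The recruitment end date, the count of 35 of 70 and the March 31, 2026 end of follow-up cannot all stand alongside a planned sample of 70

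*Protocol article*

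**What the plan says.** On timing, the Follow-Up section of the Methods says "The recruitment of patients started on November 1, 2025, and was completed by December 31, 2025", and then "All follow-up data are expected to be collected by March 31, 2026". The Abstract and the Results section repeat the November-December 2025 window in the past tense and the March 2026 end of data collection. Both also report a count: "As of January 2026, 35 of the planned 70 participants had been recruited".

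On size, Sample Size Calculation plans for a test "based on detecting a clinically meaningful between-group difference of 7.5 points". The other inputs are given as "Assuming a standard deviation of 10.58 points, a 2-sided significance level of .05, and 80% statistical power". From these, "the required sample size was 32 participants per group", and after an allowance for attrition "the final target sample size was increased to 35 participants per group, resulting in a total sample of 70 participants". The Abstract, Participants and Randomization, Treatment Allocation, and Adherence sections also give 70. No section reports a lower target, a longer recruitment period or a recalculated power.

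On visits, the interventions text fixes six weekly sessions. Data Collection and Outcome Measures places the post-treatment assessment one day after the last session and the follow-up two months after the intervention. Data Analysis makes the post-treatment NDI change the primary endpoint.

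**The concern.** A recruitment period that is over and a sample that is half full leave two possibilities, and each breaks something the article states.

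If enrolment ended at 35, the trial has half the size on which its power rests. A reader who credits a non-significant NDI result with 80% power would read far more into it than the data could bear.

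If enrolment went on towards 70, the completion date is wrong and the follow-up end date does not leave time for the second half of the sample to have the two-month visit. Every outcome in Table 2 is scheduled at that visit.

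**Working it through.** **1. Reproduce the plan's figure.** Inputs from Sample Size Calculation: difference 7.5, SD 10.58, two-sided alpha .05, power 80%.

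n per group = 2 × (1.960 + 0.842)² × 10.58² / 7.5² = 2 × 7.849 × 111.94 / 56.25 = 31.2, rounded up to 32.

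This matches the stated 32. The t-test version needs 32.2, and 32 per group gives 79.7% power. The formula is not the problem.

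**2. Branch A: recruitment closed at 35.** With 1:1 allocation the groups are 17 and 18. A loss of about 10% leaves 31 or 32 participants (31.5 exactly), so 15/16 and 16/16 are both shown.

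For groups of size a and b: SE = 10.58 × √(1/a + 1/b). Power (normal approximation) = Φ(7.5/SE − 1.960). Detectable difference at 80% power = 2.802 × SE. The t-test columns use the noncentral t.

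| Groups | SE | Power, normal | Power, t-test | Detectable, normal | Detectable, t-test |
|---|---|---|---|---|---|
| 17/18 | 3.58 | 55% | 53% | 10.0 | 10.3 |
| 16/16 | 3.74 | 52% | 49% | 10.5 | 10.8 |
| 15/16 | 3.80 | 51% | 48% | 10.7 | 11.0 |

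The planned difference is 7.5 points, which Data Analysis also uses as the clinically meaningful change.

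**3. Branch B: recruitment continued to 70.** Session 6 falls 35 days after session 1, the primary assessment one day later, and the follow-up two calendar months after session 6 (8 weeks as a lenient reading).

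| Session 1 | Session 6 | Primary assessment | Follow-up, 2 calendar months | Follow-up, 8 weeks |
|---|---|---|---|---|
| Dec 27, 2025 | Jan 31 | Feb 1 | Mar 31 | Mar 28 |
| Dec 31, 2025 | Feb 4 | Feb 5 | Apr 4 | Apr 1 |
| Jan 1, 2026 | Feb 5 | Feb 6 | Apr 5 | Apr 2 |
| Feb 23, 2026 | Mar 30 | Mar 31 | after Mar 31 | after Mar 31 |

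Anyone whose first session is in January 2026 or later therefore misses March 31 for the two-month visit on either reading. On this branch that covers the 35 participants not yet recruited. The primary assessment stays within March 31 for first sessions up to February 23.

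**4. Inside the stated window.** On calendar months, only first sessions on December 28-31 overrun, by 1 to 4 days. On the 8-week reading only December 31 does, by one day. This is minor.

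**The case against.** **No sentence says that recruitment closed at 35.** That reading joins two separate statements. The count could be outdated or mistaken, and the power loss belongs to one branch only. This stands. It does not remove the contradiction, because each branch needs a correction somewhere.

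**The 80% statement is a planning calculation and is not false.** This also stands: the calculation reproduces. A reader might infer that the power statement is simply wrong, but the document supports only the conditional claim that it would not describe a trial closed at 35.

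**March 31 is an expected date.** A reader might infer a cut-off that would delete or shorten the two-month visit for half the sample. The document sets no lock and no rule to drop later visits. What is shown is that the forecast cannot be met for those participants. The primary endpoint need not be touched.

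**The mixed model could gain power.** It might, but the article gives no baseline correlation, and it offers baseline NDI as a covariate only if imbalance appears. Suppose 10.58 is a raw-score SD and baseline is fully adjusted for, so that the SD becomes 10.58 × √(1 − r²). At 17/18, an assumed r of 0.5 gives an SD of 9.16 and 65% power; r of 0.7 gives 7.56 and 81%. If 10.58 already refers to change scores, this gain cannot be assumed.

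**The article plans no claim of no difference.** True. It plans effect sizes and comparison with minimal important differences. The risk lies in how a reader would use the stated 80%.

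**Conclusion.** The point holds as an internal contradiction. The recruitment end date, the reported count, the target of 70 and the expected end of follow-up cannot all be right.

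Its size depends on the branch. Closed at 35 means about 53% power for 7.5 points (55% by the normal approximation), 48-49% after roughly 10% loss, and a detectable difference of about 10.3 to 11.0 points. Continued to 70 means a wrong completion date and two-month visits in April 2026 or later for anyone starting from January, with the primary endpoint largely protected.

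The figures assume the article's SD, an unadjusted two-group comparison, near-equal groups and weekly sessions kept to schedule. The document does not show which branch is true. The article is dated August 20, 2026, after every date in question, so the facts should be available. The correction matters because it determines what a non-significant NDI result can be taken to mean.

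**What to change.** State one recruitment status and the number actually randomized, consistently in the Abstract, Follow-Up and Results.

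- **If recruitment continued to 70:** replace the recruitment and follow-up end dates with dates derived from the last participant's first session plus 5 weeks plus 2 months, and treat data collection as complete only after that visit.
- **If it closed at 35:** keep the planning calculation, and add to Sample Size Calculation the power for the number randomized (about 53% for 7.5 points) or the detectable difference (about 10.3 points at 80% power). Report the NDI difference with its 95% CI, and do not read a non-significant result as showing no added value.
- **If the count of 35 is itself wrong:** correct it, and check that the last first session is compatible with the March 31 date.

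The cost is wording in four places, plus either a later completion date or a less favourable power statement. No design element or outcome has to change.
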